### Development of a COPD prediction model

Associations between exacerbations with spatiotemporally resolved environmental exposure established in the Statistical associations between personal exposure with COPD-related health outcomes section will be combined with the time-activity exposure model (LHEM) to create a predictive model for COPD exacerbations across London. First, time-location-activity patterns of the COPD cohort will be compared with general population-level time-activity patterns derived from the Traffic Pollution and Health in London project.^24^ This will be used to test the applicability of general population behaviour patterns when assessing COPD associations in epidemiological studies.

The association between personal exposure to air pollution with COPD exacerbations estimated in the Statistical associations between personal exposure with COPD-related health outcomes section will form the basis of the COPD prediction model. This model will be used to create high resolution (20×20 m grid) daily COPD exacerbation risk maps for the years 2005–2011, based on modelled meteorological and pollutant conditions, coupled with typical patient with COPD time-activity patterns identified in the Activity algorithms section. The model will thus retrospectively predict days and locations more likely to trigger a worsening of symptoms and/or exacerbation in patients with COPD over this time period.

The performance of the predictive model will be evaluated using validated methods for patient identification^21^ from EHRs, CPRD, HES and ONS death data excluding data from the COPE cohort. Spatial and temporal patterns of recorded exacerbations will be compared with model risk estimates linked to the home address. If it is demonstrated that there are significant associations between model predictions and recorded exacerbations, the algorithms used will be generalised for use outside of London. These algorithms will provide an opportunity for the development of a national COPD forecasting service with proven performance in predicting increased risk of exacerbations.

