## Introduction

Chronic obstructive pulmonary disease (COPD) is a chronic progressive disease associated with the abnormal inflammatory response of the lungs to noxious particles or gases^1^ and is characterised by increased resistance to airflow in small conducting airways, changes in lung compliance and the premature collapse of airways during expiration.^2^ The inflammatory responses can lead to increased sputum production, breathlessness and reduced lung function, often resulting in reduced exercise tolerance and decreased quality of life.^3^
^4^ COPD has a large burden on healthcare resources with an estimated annual cost to the National Health Service (NHS) currently of over £800 million.^5^ At present, it is the fourth leading cause of death worldwide, and it is predicted that total deaths from COPD may increase by more than 30% in the next 10 years unless urgent action is taken to reduce the underlying risk factors.^6^

Smoking is the most important risk factor for COPD; however, an estimated 25–45% of patients have never smoked. Other risk factors include a history of pulmonary tuberculosis, chronic asthma, childhood respiratory tract infections, occupational exposure to dusts and gases, air pollution and low socioeconomic status.^7^ The prevalence of COPD is increased in individuals living close to traffic,^8^ and patients with COPD have substantial mortality risks associated with particles^9^ and temperature changes.^10–12^ Exacerbations of COPD are acute episodes of deterioration associated with increased mortality and decreased quality of life, and are the second most common cause of adult emergency medical hospital admission in the UK.^8^ Infections, both bacterial and viral, are known to play a major role in exacerbations.^4^

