In total, 160 participants will be recruited from CPRD using an algorithm containing validated COPD diagnostic codes. Patients with data in CPRD who have a diagnosis of COPD based on a validated code list by Quint *et al*^21^ are not coded for mild COPD (ie, moderate or severe patients only), are not coded as a current smoker, are aged >35 years, and have had between one and two identified exacerbations in the preceding year will be included. After running the algorithm to identify suitable participants, general practices that have agreed to participate in research through CPRD will be sent a list of the potential participants. GPs will confirm to CPRD the suitable patients identified previously using the Vision Identification. CPRD will then send participant information packs to the general practices to disseminate to the potential recruits. The information pack will contain a cover letter from the general practitioner introducing the study, a participant information sheet with detailed information of what the project entails, and an expression of interest form that participants can complete and send to the research team in a prepaid envelope. Once received, the research team will then be able to contact the participant to enrol them in the study through a clinic appointment. Participants will also be recruited from respiratory clinics in secondary care as an additional recruitment option.

The sample size of 160 patients is based on the estimated number of exacerbations for the cohort. Since we will recruit with a bias towards patients with COPD with a history of COPD exacerbations, we have made the conservative estimate that we will capture at least 200 exacerbations with a cohort of 160 patients. We have calculated a minimum detectable relative risk (RR) to detect associations at p<0.05 with 80% power. With 200 exacerbations, this will permit detection of about RR=1.65 in the highest 20% of days compared with others (RR=2.00 in the highest 10%). Other more common outcomes and in particular peak flow will have power to detect smaller associations.^22^

Two secondary recruitment methods will be established to make up any shortfall in recruits through the CPRD: recruitment from respiratory clinics in local hospitals and presentations at British Lung Foundation ‘Breathe Easy’ respiratory disease support groups.

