### Statistical analysis

Survival analyses for repeated measurements will be performed on the basis of the Cox proportional hazards model. Interval censoring for handing ties over appropriate event time intervals will be applied specifying each participant to a stratum. Essentially, conditional regression will be used to estimate the HR of subjective health symptoms and exacerbations in relation to seasonal variations of personal exposure (prognostic factor). The conditional regression models will be developed by the PHREG procedure in SAS V.9.3 (North Carolina, USA) with robust sandwich covariance for aggregated data. Ties will be handled with the DISCRETE method. Medication use will be inserted as a control factor in the models.

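### The cohort estimate is within-person, yet it drives risk maps by location, and the rule for extending the model beyond London can be met by spatial association with no trigger effect

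*Protocol article*

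**What the plan says.** - **Statistical analysis.** Exacerbations and symptoms are analysed by conditional Cox regression, "specifying each participant to a stratum". The exposure factor is described as seasonal variation in personal exposure.
- **Recruitment of panel participants.** Power is stated for high-exposure days against other days: with 200 exacerbations, RR about 1.65 for the top 20% of days and 2.00 for the top 10%, to "detect associations at p<0.05 with 80% power".
- **Development of a COPD prediction model.** The cohort association is the basis of daily risk maps on a 20×20 m grid for 2005–2011. The claim is: "The model will thus retrospectively predict days and locations more likely to trigger a worsening of symptoms and/or exacerbation in patients with COPD". The test uses records that exclude the COPE cohort: "Spatial and temporal patterns of recorded exacerbations will be compared with model risk estimates linked to the home address". If significant associations are shown, the algorithms are to be extended beyond London, with a national forecasting service in view.
- **Introduction.** "The prevalence of COPD is increased in individuals living close to traffic", and low socioeconomic status is listed among the risk factors for COPD.
- **Use of EHR to analyse exacerbations.** Covariates and comorbidities are given in Figure 3, which is not shown. The same comparison with historical records is announced there.

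**The concern.** Conditioning on participant is a sound way to study triggers, because fixed personal confounders drop out. It also removes whatever is constant for a person, including the home and its neighbourhood. The maps then rank places as well as days, and the external test pools the two.

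A comparison across home addresses is open to every difference between residents of different areas. The rule for extension does not ask that the temporal part succeed by itself. A model whose trigger association is false could therefore pass on residential differences alone and go forward as the basis of a national service.

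**Working it through.** **1. The plan's own figure confirms the contrast.** Inputs from Recruitment of panel participants: 200 events, share of high days a = 0.20 or 0.10, 80% power, p<0.05 (taken as two-sided; the article does not say). Minimum RR = exp[(1.960 + 0.842) / √(200·a·(1−a))].
- a = 0.20: exp(2.802/√32) = exp(0.495) = 1.64, against 1.65 stated.
- a = 0.10: exp(2.802/√18) = exp(0.660) = 1.94, against 2.00 stated, which is slightly cautious.

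The first figure reproduces. The quantity that the study is powered for is high days against other days.

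**2. What the stratum removes.** Write the exposure of person i at time t as h_i + d_it, with h_i the part that is fixed by the home, and the hazard as α_i·exp{β(h_i + d_it)}. For an event at time s, the stratum contributes exp{β(h_i + d_is)} / Σ_t exp{β(h_i + d_it)} = exp(β·d_is) / Σ_t exp(β·d_it). Both α_i and h_i cancel.

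Simulation check (assumed: 160 people, 182 days, about 200 events, between-home RR 1.30 per SD, daily RR 1.00, equal variance between homes and between days, 100 runs):
- stratified by participant: mean RR 1.01;
- unstratified: mean RR 1.15. About exp(½·ln 1.30) = 1.14 is expected, since half of the exposure variance lies between homes.

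The stratified model is neither biased by differences between homes nor informative about them.

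**3. The external test with zero trigger effect.** All inputs are assumptions: 500 areas, about 50 patients per area, 1.5 exacerbations per patient-year, one year, 300 runs. Expected events: 500 × 50 × 1.5 = 37,500.

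Share of tests with p<0.05:

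| Assumed gradient per SD of spatial exposure | Area counts | Per COPD patient | Day-to-day only |
|---|---|---|---|
| None | 25% | 3% | 4% |
| Prevalence 1.02 | 85% | 6% | 6% |
| Prevalence 1.05 | 100% | 7% | 6% |
| Prevalence 1.10 | 100% | 4% | 2% |
| Prevalence 1.20 | 100% | 4% | 5% |
| Per-patient rate 1.02 | 88% | 97% | 5% |
| Per-patient rate 1.05 | 100% | 100% | 5% |
| Per-patient rate 1.10 | 100% | 100% | 6% |

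The 97% can be checked by hand. The standard error of the log rate ratio per SD is about 1/√37,500 = 0.0052. Then ln 1.02 / 0.0052 = 0.0198/0.0052 = 3.8, and Φ(3.8 − 1.96) = 0.97.

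**4. Limits of the simulation.** The count test is overdispersed (25% rejection with no gradient), so its 85% is partly inflated. The day-to-day test was run without seasonal confounding. In real data it needs a short calendar window to keep its error rate.

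**The case against.** **Denominator.** The evaluation relies on validated identification of patients, and the predicted risk is for people with COPD. This may mean that COPD patients are the denominator. If so, higher prevalence near traffic does no harm: the per-patient column stays at 4–7% under a prevalence gradient. This stands. A reader might infer from the Introduction that exacerbations must cluster in polluted cells. The article does not support that, because traffic proximity, deprivation and smoking are named there as correlates of having COPD and not of the exacerbation rate per patient.

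**Adjustment.** Figure 3 may list smoking, deprivation or severity, and its mention directly precedes the announcement of the same comparison. One cannot say that adjustment is absent. Nor can one count on it to remove all residential differences at this sample size.

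**Extrapolation.** A within-person effect may be applied to exposure at other places if the effect is the same everywhere. The maps use typical time-activity patterns and do not claim to estimate differences in baseline risk between residents. This also stands. A reader might infer that the location claim has no support at all. That goes too far: it has support conditional on an assumption that the cohort cannot check. Personal monitors also follow people between places, so the contrasts are not purely day-to-day.

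**Level of detail.** Temporal patterns are part of the planned comparison, and an article may leave the modelling to a fuller document. But the rule for extension is printed in the article, and as printed it does not require temporal success.

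**Conclusion.** The point holds in this form. The cohort gives within-person contrasts only, and the stated test pools spatial with temporal agreement, so it can be passed by the spatial part with no trigger effect. Two routes lead there: patient numbers that differ by residence, if no COPD-patient denominator is used, and per-patient exacerbation rates that differ by residence, for example through deprivation or severity.

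The article gives no figure for either gradient. The conclusion on size is conditional: under the assumed inputs, a rate ratio of 1.02 per SD is enough for near-certain significance, while a temporal test stays at 2–7% throughout. What does not depend on those inputs is the algebra of the stratum and the wording of the rule. The change should be made before the evaluation is run.

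**What to change.** In Development of a COPD prediction model:

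1. Make the criterion for extension beyond London a within-patient temporal comparison in patients outside the COPE cohort: modelled risk at the home cell on exacerbation days against the same patient's other days in a short calendar window.
2. Report the between-location comparison separately as secondary, per identified COPD patient and adjusted for the available smoking, deprivation and severity data.
3. State that locations are an extrapolation of the within-person effect, which the temporal test does not verify. The word need not be dropped if it is labelled so.

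The records are already planned, so the cost is a little more analysis and a change of wording. The downside is a narrower validated claim: the evaluation would support statements about when risk rises, and the ranking of places would stay unverified.

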The methodology presented here will allow development of forecasting models that can be used to predict times of increased exacerbation risk. This will aid healthcare providers and allow more accurate planning and allocation of resources which will reduce costs for the NHS. It will aid patients as it may provide an opportunity to alter behaviour and to prevent exacerbations from occurring. By providing a more robust evidence base, policymakers may be able to take more targeted and efficient decisions on reducing environmental risk. Members of the public will be able to make more informed decisions on how to minimise their own risks, improving health and quality of life.

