## Ethics and dissemination

CPRD has been granted Multiple Research Ethics Committee (MREC) approval to undertake observational studies and external data linkages with HES and ONS. Research and Development (R&D) approval has also been granted by the Royal Brompton and Harefield NHS Foundation Trust and Guy's and St Thomas' NHS Foundation Trust to carry out the study at the Clinical Research Facility in the Royal Brompton Hospital and the Lane Fox Respiratory Unit at St Thomas' Hospital (IRAS ref 166785). Ethical approval is being sought to collect blood and sputum samples from a subset of 20 participants for a pilot study.

Participants will be informed that the monitors use GPS technology and will provide spatial data at intervals during the day. Participants will be reassured that this information will only be accessed at the end of the study to analyse overall spatial and temporal relationships and not real-time movement. In addition, participants will be informed that the monitors will have a built-in microphone for the purpose of recording ambient (background) noise levels. It will not be used for the recording of speech.

The behavioural and environmental COPD associations identified during the study will be adapted for application on a national scale and disseminated to healthcare providers including the Department of Health, Clinical Commissioning Groups and GPs. Information will include evidence of environmental conditions and patient activities that are found to contribute to an increased risk of COPD symptoms and exacerbations. The predictive algorithms will be made available, allowing the development of a validated national COPD forecasting system. Such a system has the potential for further commercial exploitation and the research team will seek to collaborate with the UK Meteorological Office in order to improve the effectiveness of their Healthy Outlook service. This research would provide an opportunity to carry out a cost–benefit analysis of such a system, now essential for commissioning in the current health market.

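### The prediction model is evaluated only retrospectively on 2005–2011 conditions, which cannot support a forecasting service described as proven or a forecasting system described as validated

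*Protocol article*

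**What the plan says.** In the Protocol article, the section *Development of a COPD prediction model* combines the panel's exposure–exacerbation associations with the London Hybrid Exposure Model. The product is "daily COPD exacerbation risk maps for the years 2005–2011, based on modelled meteorological and pollutant conditions". The direction is stated openly: "The model will thus retrospectively predict days and locations more likely to trigger a worsening of symptoms".

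Performance is judged on records "from EHRs, CPRD, HES and ONS death data excluding data from the COPE cohort", and the comparison is this: "Spatial and temporal patterns of recorded exacerbations will be compared with model risk estimates linked to the home address". The condition for going further is "If it is demonstrated that there are significant associations between model predictions and recorded exacerbations". If it is met, the algorithms are to be generalised beyond London and to give an opportunity for "development of a national COPD forecasting service with proven performance in predicting increased risk of exacerbations".

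Two later sections build on this. The Discussion says the methodology "will allow development of forecasting models that can be used to predict times of increased exacerbation risk", and expects providers to plan resources and patients to change behaviour accordingly. The section Ethics and dissemination says the algorithms will be released, "allowing the development of a validated national COPD forecasting system".

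**The concern.** A warning service ranks a day before it happens, from what is known or predicted at the time of issue. The evaluation described ranks past days from conditions modelled after the fact. No forecast input, prospective period or stated lead time appears in it. Meeting the stated criterion would show that modelled conditions and recorded exacerbations go together. It would not show that a warning issued beforehand picks out the right days.

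The results are to be disseminated to the Department of Health, commissioning groups and GPs. If they are described as proven or validated for forecasting, those readers will take retrospective performance as the performance of an advance warning. Under the assumption that forecast inputs carry more error than retrospective ones, that reading is too favourable.

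**Working it through.** **1. Evaluation and claim side by side.**

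| Element | Evaluation described | Forecasting claim needs |
|---|---|---|
| Days judged | Past days, 2005–2011 | Days still to come at the time of issue |
| Inputs | Modelled meteorology and pollution, typical COPD activity patterns, home address | Inputs available at the time of issue |
| Lead time | Not stated | Stated |
| Criterion | Significant association | Performance at that lead time |
| Population | Records outside the COPE cohort | Also outside the cohort |

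The last row is satisfied. The first four are not, with one possible exception. The section *Statistical associations between personal exposure with COPD-related health outcomes* lists lag effects, cumulative exposure and rate of change among the explanatory variables. If only lagged terms are retained, the inputs precede the day at risk and some lead time is built in. The prediction section does not say which terms are carried forward.

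**2. The plan's own figure.** The only effect sizes in the article are the minimum detectable relative risks under *Recruitment of panel participants*: 1.65 for the highest 20% of days and 2.00 for the highest 10%, with 200 exacerbations, p<0.05 (taken as two-sided) and 80% power. By the Schoenfeld formula, events = (1.960 + 0.842)² / [a(1−a)(ln RR)²], where a is the share of high days:

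- a = 0.20, RR 1.65: 7.849 / (0.16 × 0.2508) = 196 events. The minimum detectable RR at 200 events is exp(2.802/√32) = 1.64, so the stated 1.65 is reproduced.
- a = 0.10, RR 2.00: 7.849 / (0.09 × 0.4805) = 182 events. The minimum detectable RR at 200 events is exp(2.802/√18) = 1.94, so the stated 2.00 is somewhat conservative.

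The point does not rest on these figures. They serve below only as an effect size.

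**3. Illustration of the direction.** Assumptions: forecast and retrospective exposure are bivariate normal with correlation r; each flags the same share a of days as high; risk depends only on whether the retrospective exposure is high. The article gives no r. Let h be the share of forecast-high days that are high retrospectively, and f the share of the remaining days that are high, so f = a(1−h)/(1−a). Then

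RR on forecast-high days = [1 + (RR−1)h] / [1 + (RR−1)f].

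For a = 0.20 and RR 1.65:

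| r (assumed) | h | f | RR on forecast-high days | Excess kept, (RR−1)/0.65 |
|---|---|---|---|---|
| 0.9 | 0.750 | 0.063 | 1.4873/1.0407 = 1.43 | 66% |
| 0.7 | 0.565 | 0.109 | 1.3669/1.0708 = 1.28 | 43% |
| 0.5 | 0.436 | 0.141 | 1.2832/1.0917 = 1.18 | 27% |

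For a = 0.10 and RR 2.00, the same r values give 1.63, 1.39 and 1.23.

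**4. The criterion.** Even with no forecast error (r = 1), an RR of 1.65 puts 0.2 × 1.65 / (0.2 × 1.65 + 0.8) = 0.33/1.13 = 29.2% of events on the top 20% of days. An association of that size could be significant in a large record set while separating days only modestly. The article gives no size for the evaluation data.

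**The case against.** The strongest reply is that forecasting is later work. Stage 5 in the abstract is only the development of a prediction model for London. The service is conditional on the associations being found and is worded as an opportunity. Collaboration with the national weather service is something the team will seek. Checking the exposure–risk algorithm on past conditions before adding forecast inputs is a sensible order of work, and excluding the COPE cohort makes the check external. All of this stands, so not testing a forecast at this stage is a legitimate choice of scope. It does not rescue the two adjectives: the condition attached to proven performance is itself a retrospective association, and the dissemination section says validated without restating any condition.

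It can also be said that lead times, input sources and skill measures belong in a fuller document. As missing detail they are no finding. The point here is a conclusion that the article states and that its stated evaluation cannot bear.

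Three stronger readings are tempting, and the article does not support them.

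- A reader might infer that the team plans to report forecast skill from the hindcast, or that no lead time can exist. The text calls the prediction retrospective, and lagged exposures are allowed.
- A reader might infer that each day's exposure is already known. It is modelled, so the hindcast carries exposure error of its own. The article does not say outright whether the inputs are analyses or archived forecasts, though nothing suggests forecasts.
- A reader might infer that the contrast largely disappears in forecast use. In the illustration 66% of the excess risk is kept at r = 0.9 and 43% at r = 0.7, and nothing in the article favours a low r.

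**Conclusion.** The concern holds as a mismatch between evaluation and conclusion. The planned comparison can support a statement about retrospective risk ranking in patients outside the cohort. It cannot support proven forecasting performance or a validated forecasting system, unless the retained associations use only lagged exposures, which is left open.

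Only the direction of any overstatement follows, and only if forecast inputs carry more error than retrospective ones. Its size cannot be obtained from the article. The values 1.43, 1.28 and 1.18 rest on an assumed correlation, on bivariate normality, and on a minimum detectable RR for the 160-patient panel, which is not an expected result in the external records. The panel study of personal exposure and exacerbations is unaffected.

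**What to change.** **Wording (sufficient).** In *Development of a COPD prediction model* and in *Ethics and dissemination*, limit proven and validated to retrospective (hindcast) performance. In the Discussion, describe forecasting as still to be tested. State in the prediction section which exposure lags the model carries forward, since that decides whether any lead time is present.

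**Analysis (preferable in addition).** Add to the prediction section a run on the same external records in which the risk for day t uses only exposure and meteorology up to day t−1. Report it beside the hindcast as a conservative lead-time benchmark. Use archived forecasts only if they are available; the article does not say that they exist for 2005–2011.

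**Cost.** The rewording needs no new data. The additional run is one more analysis of records already planned for use, and the reported performance is likely to look less favourable. The t−1 run measures what can be had from persistence, so it may understate a service that uses real forecasts, and it should be labelled accordingly.
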